
#### Household cost data

Household expense data will be collected during the last nine months of the study at each site to capture the out-of-pocket expenditures that households incur during the treatment of enrolled SYI under both treatment arms for RCT1 and RCT2. Data will be collected from at least 10% of SYIs enrolled under each arm at each site. These sampled households will be assumed to be representative of all treated YIs both temporally and geographically. Further, the household data for the seven-day treatment period will be collected either on day eight or 15 of the outcome visit or at most within two weeks from the last outcome assessment, to avoid recall bias. Where available, caregiver-reported expenditures will be cross-checked with receipts or facility payment records to enhance accuracy.Standardised household questionnaires will be used across all sites to collect data on medical and non-medical costs using the REDCap tool [25,26]. Training will be provided to collect data using these forms, and pilots will help improve the tool and data quality. Data inconsistencies will be identified, discussed with the sites and corrected at the analysis stage.Data will be collected on the type of treatment arm and duration of treatment. Direct treatment costs for each component will be collected in local currency from sampled households in each treatment arm for RCT1 and RCT2 at each site. Total medical expenses by households will be collected for registration and consultation fees, expenditures on medicines such as amoxicillin, ampicillin, gentamicin and other supportive care such as paracetamol, consumable supplies such as syringes, needles, canulas, bandages, spirits, gloves, laboratory expenses such as x-ray, blood work, urine tests (investigation costs), or any other payments to hospitals. Non-medical expenses, such as transport and food, will be recorded for seven days. Data will include the mode of transportation and expenses incurred by any household member on round-trip trips during the treatment period. Similar information will be collected on food, with the amount spent outside the home during the days the infant had to stay at or visit the hospital.Indirect expenses are opportunity costs, or the costs incurred by the household in terms of wage loss to take care of the sick child. Data will be collected from parents and caretakers who lost their wages due to time spent caring for the child. Household work that does not entail income will not be included in the opportunity cost. Data will be collected on the type of occupation/source of income, average earnings on a daily, monthly, or yearly basis (in the provided ranges), and the number of days not able to work to take care of the SYI. Maximum seven days of wage loss will be considered.

### Statistical analysis procedures

The statistical analysis for the hospital cost data will be done in Microsoft Excel (Microsoft, Redmond, WA, USA). The data from all facilities where infants are randomised will be entered into a structured Excel document. The average costs per SYI for staff, medicines, consumables, and inpatient bed costs, will be calculated as outlined below. Mean, median, and 95% confidence intervals will be calculated using t-values per SYI receiving recommended or partial treatment for each of the cost variables at the hospital, as well as at the household level. The medical treatment costs per SYI will be the sum of the weighted average of staff costs, medicines, consumables, inpatient bed costs, and operational costs, where weights are infant-days for those receiving recommended and partial treatment. Non-medical costs on transport, food and wage loss per SYI will be added to total medical costs per SYI to estimate the total societal costs for the control and intervention arms for RCT1 and RCT2 separately. Household payments for both medical and non-medical treatment would be added to calculate the household burden in total societal costs.

The treatment outcomes for all enrolled in the control and intervention arms will be used to estimate incremental CE ratios (ICERs) for both RCTs.

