Coverage of sick YIs (SYI) assessed, enrolled and treated under both RCT1 and RCT2 for control and intervention.Data on two outcome variables for all SYI covered under different treatment arms. Well-trained independent outcome assessor visits all enrolled cases on days two (only for RCT1), four, eight, and 15 after the initiation of treatment to assess the study outcomes in both intervention and control arms.Average annual salaries of nurses, paediatricians, medical officers and any other staff supporting treatment. To calculate staff costs per minute, data will be collected on the average number of days in a month and the average number of hours in a day that staff work.Staff time will be considered only for activities that are linked to hospital staff and not those linked to research staff, such as outcome assessment or treatment documentation (**Table 1**, **Table 2**). The activities for the staff time will be based on a pre-defined implementation strategy [21,22].Data will be collected for SYI that receive at least 80% of the treatment (recommended treatment) and those who receive <80% of seven-day (<5.5 days) treatment (partial treatment). The latter occurs due to a treatment failure, a change in treatment, readmission, left voluntarily, or death. For the recommended treatment, we will collect costs for the seven-day treatment period following the initial assessment, across both study arms and both trials. For partial treatment, medical costs will be calculated for an average treatment period of three days in RCT1 after the initial assessment, and for two days in RCT2 in both inpatient and outpatient arms after randomisation. Costs for enrolled SYI will be weighted by the proportion of participants receiving 80% recommended treatment and those receiving partial treatment, with weights set to SYI for each group. This prevents any child randomised and enrolled from being missed. Costs due to complications, changes in treatment, and/or readmission are outside the seven-day recommended treatment window in both study arms of both trials and will not be collected.Data on staff time per visit for an activity and the number of visits undertaken for each activity during the recommended treatment period will be collected by interviewing at least 3–5 staff of each type at each hospital.The staff time for all visits during the treatment period will be weighted by the number of days an infant receives the activity and the number of YI receiving the activity (defined as weighted by infant days). For the first activity assessment on presentation at the hospital, the number of SYI will be all enrolled for a given treatment, whether partial or recommended. For all other activities, SYI who receive 80% recommended treatment will be considered to have received seven days of treatment, and those receiving partial treatment for an average of three days to calculate the costs for those enrolled.The average exchange rate used to convert all the cost estimates in local currency into USD will be for 2024, the period for which the salaries of providers, prices and household costs will be reported. It will ensure consistency, and inflation rate adjustments will not be needed for cost calculations. The recommended treatment period will be seven days for inpatient treatment in the control arm and seven days for outpatient treatment in the intervention arm for RCT1. For RCT2, the average length of inpatient treatment is 48–72 hours, prior to a negative CRP laboratory test. In RCT2, the control group after randomisation will continue receiving inpatient care for five days, while the intervention group will be discharged from the hospital on oral amoxicillin for five days to be taken at home. Both arms will share the initial hospitalisation costs during the first two days in RCT2, including CRP test costs (including staff time, kits, and laboratory costs).The data on quantities used of injection gentamicin, injection ampicillin and oral amoxicillin will be as per the recommended treatment and partial treatment per SYI for each treatment arm under each RCT.The number of SYI receiving specific medicines and consumables for each arm under both RCTs will be calculated based on the numbers receiving recommended treatment and those receiving partial treatment.Information on types and quantities of consumables required with each medicine will be collected separately for each hospital and each arm under both RCTs. The cost of medicines and consumables will be charged per size in which they are dispensed. Medicine dosage varies with the weight of the YI [21,22]. Price will be taken for full strength, and the rest will be marked as wastage. Price data will be taken from the hospital's pharmaceutical department (if available); otherwise, the market price or the WHO price will be used.Data on annual financial expenditures and admissions in the newborn intensive care units or paediatric wards where YI with PSBI are treated as inpatients at the hospital will be collected and allocated based on patient days to calculate the inpatient bed costs/ SYI treated as an inpatient. These expenditures include administration, utilities, laundry, security, data management, internet, non-consumables and other costs in the hospital inpatient ward.Hospital ambulance to transport enrolled SYI under a specific treatment arm is a cost to the hospital. It is difficult to get this information separately for each enrolled SYI under different treatment arms from the hospital data. Indirect estimation based on the average trip cost and the number of SYI using free public ambulances, estimated from household data for each treatment arm in RCT1 and RCT2, will be used.Hospital data will also be collected for operational costs, which help to strengthen the assessment, identification, and treatment of SYI with PSBI. These include training, supplies, and communication. The total costs under these three will be estimated per SYI assessed. Staff training costs include the costs of development of training material and training cost per staff per day based on the per diems, honorarium for trainers, venue and refreshment costs. Total training costs will be calculated for all staff who were used to assess and treat SYI and will be estimated per SYI assessed. Training costs for research staff for outcome assessment or data collection will not be collected or included. Price and quantities of supplies used during the assessment, such as timers, thermometers and weighing scales, will be prorated for PSBI assessed. Communication costs, include job aids or educational material, and the cost of videos developed and played at the hospitals for educating the mothers about the danger signs. Data will be collected on item quantities and prices from hospitals to assess total costs and costs per SYI assessed.

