
### Estimation of medicines and consumables costs

The following steps will be followed to calculate the medicines and consumable costs per SYI at a given site:

For each medicine used under a given arm for a given trial, the total cost of a medicine for each SYI will be calculated by multiplying the price per vial or tablet for a medicine (P) by the quantities of medicines required per SYI (Q) for recommended treatment and the number of infants receiving the medicine (n). Average medicine quantities will differ by age and weight of the SYI [21,22], and there will be associated wastage when standard-sized injectables or tablets are used. For the hospitalised SYI, injection ampicillin is given twice daily in the first week of life, thrice daily in 2–4 weeks of life, and four times daily in four or more weeks of life. 500 mg vials will be used to draw the required doses based on the SYI’s weight and age. Assuming an average dose of 200 mg three times a day, at least two vials per day will be needed for a SYI, totalling 14 vials over seven days. With a daily requirement of 600 mg, the average wastage is 40%; at higher weights, it decreases to 25%. For gentamicin, an ampoule of 40 mg/ml or 20 mg/2 ml will be used, from which 8 mg, 16 mg, or 24 mg will be administered once daily, depending on the YI’s weight. Assuming an average requirement of 16 mg, seven ampoules of 20 mg will be needed for the control arm and two ampoules for the intervention arm in both RCT1 and RCT2. This would lead to an average wastage of 20%. For amoxicillin, 14 dispersible tablets of 250 mg will be required for seven days of treatment in RCT1 and 10 dispersible tablets for five days as an outpatient in RCT2. SYI <4 kg will require half a tablet, and those weighing >4 kg will require a full tablet. We assume, on average, 14 tablets will be dispensed for each SYI. Assuming half the SYIs are <4 kg and that, on average, only half a tablet is used from those dispensed, there would be 25% wastage.For each medicine at each hospital, the cost of each consumable will be calculated by multiplying the price per unit of the consumable (Pc) by the consumable quantities required per SYI (Qc) for recommended treatment with that medicine, and the number of infants receiving the consumable (n).The total cost of medicines will be estimated by adding the costs of all medicines at a given hospital that are needed for each arm for each RCT.Similarly, the total cost of the consumables will be estimated by adding the costs of all consumables corresponding to the medicines needed for each of the arms under the two trials at a given hospital.A few consumables are not linked to specific medicines but are related to the treatment of SYI, such as a cannula fixer, a cannula for intravenous injections, gloves, and CRP kits for protein laboratory test. These costs will also be calculated by multiplying the price per unit of the consumable (Pc) with consumable quantities required per SYI (Qc) for recommended treatment with that medicine, and the number of infants receiving the consumable (n) at the hospital.The total cost of consumables will be estimated by adding the costs of all consumables at a given hospital needed for each arm under the two trials.The total costs of medicines and consumables (estimated separately) at each site will be calculated by adding the costs at each hospital for each arm under the two trials.Average weighted medicine and consumables costs at a site will be calculated by summing the costs of all medicines and all consumables (separately) across all hospitals for each treatment arm. These total costs of medicines and consumables (estimated separately) will be divided by the number of SYI receiving recommended treatment at each hospital within a site to estimate medicine and consumable costs per SYI.For partial treatment, we will follow the same procedure (in steps 1–8) as for recommended treatment. Medicines and consumables will be calculated for three days for RCT1 and for two days after randomisation for RCT2. All medicines and consumables during the first two days of inpatient treatment will be common to both the recommended and partial treatment for RCT2.

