### Site-wise and combined analysis plan

While site-wise analyses will provide insights into differences across study sites, results will also be presented for all sites combined and separately for the Asia and Africa regions. Variations in care pathways will be addressed through hospital-level stratification of staff, medicine, and consumable costs, using infant-days as weights to derive site averages. Costs for partial treatment will be estimated at the hospital level by using infant-days as weights for infants receiving partial treatment. Overall costs for enrolled infants will be estimated at the site level using the weighted average of those receiving recommended treatment and those receiving partial treatment. The combined average across all sites will be estimated by using enrolled infants at each site as weights for each treatment arm. The number of infants receiving at least 80% of the recommended treatment in each treatment arm will be used as weights to estimate the combined average hospital costs for the recommended treatment across all sites.

Average weighted inpatient bed costs at the site level will be estimated across all hospitals for each treatment arm using the number of SYIs enrolled in paediatric and newborn wards as weights. Combined inpatient bed costs will then be estimated using the total number of SYIs enrolled in these wards as weights at each site. Average operational costs will also be stratified at the hospital level within each site by using the number of SYIs assessed as weights, and site-stratified for combined analyses using the number of SYIs enrolled as weights at each site.

Average household costs – including registration, food, transport, and wage loss per SYI – will be calculated at the site level using the household survey sample size as the denominator. For pooled analyses, enrolled SYIs will be used as weights across sites. Both the median and the arithmetic mean will be reported to describe the distribution of costs for each variable. Uncertainty in CE will be presented using site-level, regional-level, and pooled ICERs plotted on CE planes. In addition, the mean INB will be estimated and pooled across sites, and 95% confidence intervals will be derived using the *t*-distribution based on site-level variation. An INB greater than zero will indicate that the intervention is cost-effective at the specified willingness-to-pay threshold.

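### Cost per enrolled infant combines full and partial courses by infant-days in one section and by number of infants in another; infant-day weighting, taken literally, overstates mean cost

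*Protocol article*

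**What the plan says.** The protocol article costs two groups separately in each arm: infants who received at least 80% of treatment (recommended) and those who received less (partial). It then combines them into a cost per enrolled infant. The combining step is described three times:

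- **Statistical analysis procedures:** medical cost per infant is the sum of weighted averages of staff, medicine, consumable, bed and operational costs, "where weights are infant-days for those receiving recommended and partial treatment".
- **Hospital data:** costs for enrolled infants are weighted by the share in each group, "with weights set to SYI for each group".
- **Site-wise and combined analysis plan:** "Overall costs for enrolled infants will be estimated at the site level using the weighted average" of the two groups, with no unit named for the weight.

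Course lengths are assigned. Under Hospital data, "SYI who receive 80% recommended treatment will be considered to have received seven days of treatment". Partial courses are first costed at three days in RCT1 and two days after randomisation in RCT2. Estimation of medicines and consumables costs repeats this: "Medicines and consumables will be calculated for three days for RCT1 and for two days after randomisation for RCT2". A later sentence under Hospital data, on staff activities after the first assessment, takes "those receiving partial treatment for an average of three days to calculate the costs for those enrolled" and does not limit this to RCT1.

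**The concern.** A mean cost per infant gives each infant weight one. A full course already costs more because it is longer. Weighting it again by its days counts length twice and pulls the mean towards the full-course cost. The error is larger in an arm with more partial courses, at any plausible partial share.

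The arms could well differ in that share. The protocol lists treatment failure, change of treatment, readmission, leaving voluntarily and death as reasons for a partial course, and the arms differ in place of care. The arm means form the cost difference Δc in every site, regional and pooled ICER and incremental net benefit. Two analysts following different sections of this text would report different primary results.

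The two-day and three-day statements raise a similar problem for RCT2: the text does not fix how many days of staff time a partial course is charged.

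**Working it through.** **Inputs.** From the protocol article: 7 and 3 days for recommended and partial courses in RCT1; 5 and 2 days after randomisation in RCT2, the window that the CEA section uses for the ICER. Not given, so assumed: the partial share p (5% to 30%) and a constant cost of 1 unit per treatment day. The article states no figure that could be reproduced.

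**Does another section settle the weight?** Estimation of staff costs divides total cost by the number of infants with recommended treatment, then repeats the step for partial treatment. Estimation of medicines and consumables costs does likewise. Each yields a per-infant cost *within* a group; neither says how the two are combined.

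**Formulas.** With lengths dr and dp and cost equal to days:

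- Infant weights: M1 = (1−p)·dr + p·dp
- Infant-day weights: M2 = [(1−p)·dr² + p·dp²] / [(1−p)·dr + p·dp]
- Excess: M2 − M1 = Var(d)/mean(d), never negative

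Example, RCT1, p = 20%: M1 = 0.8×7 + 0.2×3 = 6.20. M2 = (0.8×49 + 0.2×9)/6.20 = 41.0/6.20 = 6.61. Excess 6.7%.

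| p | RCT1 M1 | RCT1 M2 | Excess | RCT2 M1 | RCT2 M2 | Excess |
|---|---|---|---|---|---|---|
| 5% | 6.80 | 6.91 | 1.6% | 4.85 | 4.94 | 1.8% |
| 10% | 6.60 | 6.82 | 3.3% | 4.70 | 4.87 | 3.7% |
| 20% | 6.20 | 6.61 | 6.7% | 4.40 | 4.73 | 7.4% |
| 30% | 5.80 | 6.38 | 10.0% | 4.10 | 4.56 | 11.2% |

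In RCT1 the relative excess rises with p up to about 70% and then falls.

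**One-off costs.** Adding 2 units of fixed cost per infant in RCT1 lowers the excess to 2.5% at p = 10% (8.82 versus 8.60) and 5.0% at p = 20% (8.61 versus 8.20).

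**Effect on Δc.** For scale only, take full-course costs of USD 55 (control) and USD 18.5 (intervention). These are background figures from outside studies in the introduction, not arm costs in these trials. A partial course is costed at 3/7 of a full one.

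| Partial share, control / intervention | Δc, infant weights | Δc, infant-day weights | Saving |
|---|---|---|---|
| 10% / 5% | −33.9 | −35.3 | overstated by about 4% |
| 30% / 5% | −27.6 | −31.9 | overstated by about 15% |
| 5% / 30% | −38.1 | −37.4 | understated by about 2% |

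**RCT2, three days instead of two.** If applied to all daily costs, the post-randomisation mean (infant weights) goes from 4.85 to 4.90 (+1.0%) at p = 5%, from 4.70 to 4.80 (+2.1%) at 10%, and from 4.40 to 4.60 (+4.5%) at 20%. Counting from admission does not reconcile the two statements: two shared inpatient days plus two makes four, not three.

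**Charging seven days at the 80% boundary.** 0.8 × 7 = 5.6 days, and 7/5.6 = 1.25. An infant exactly at the boundary is charged 25% too much on strictly daily items.

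**The case against.** The strongest reply is that infant-days are meant only as a quantity multiplier. Hospital data describes the weighting as days times "the number of YI receiving the activity (defined as weighted by infant days", applied to staff time, and the costing steps then divide totals by infants. On that reading p = 20% in RCT1 gives 6.20 and nothing is counted twice. Infant-day weights are also harmless within a group, because every infant in it is assigned the same number of days. The instruction "Costs for partial treatment will be estimated at the hospital level by using infant-days as weights for infants receiving partial treatment" therefore does no damage.

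This stands in part. It shows that a correct calculation is available and may be intended. It does not remove the conflict, because the sentence under Statistical analysis procedures names infant-days for both groups together.

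Three stronger conclusions are tempting but not supported:

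- *That an arm will be over-costed.* This follows only if the infant-day sentence is applied literally to per-infant group costs.
- *That fixed lengths erase every arm difference in days of care.* The arm-specific shares of recommended and partial courses still enter the mean, and bed costs are adjusted for average length of stay. Only differences within a category are lost. Fixing partial courses at three or two days may err either way, since actual lengths are not given.
- *That RCT2 staff time is costed at three days.* An earlier sentence in the same section sets partial medical costs in RCT2 at two days, and the later one names no trial. This is an unresolved conflict, not a stated rule.

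It is also fair that costs are not purely daily. The first assessment is one-off, and in the RCT1 intervention arm the two gentamicin days fall within a three-day course.

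**Conclusion.** The protocol names two different weights for its central cost quantity, and no other section resolves the combining step. Applied as written, the infant-day rule overstates an arm's mean cost by about 4% or less at partial shares up to 10%, and by 10.0% (RCT1) or 11.2% (RCT2 after randomisation) at 30%. These figures assume purely daily costs and the protocol's own assigned lengths; one-off costs reduce them. A reader might infer that the intervention's saving is overstated by about 15%, but that needs the assumed 30% versus 5% shares and outside cost figures. Other shares give about 4%, or a small understatement, so neither the size nor the direction of the effect on Δc can be fixed from the document. The RCT2 two-day and three-day statements are a separate, smaller inconsistency, worth about 1.0% to 4.5% of the post-randomisation mean at partial shares of 5% to 20%.

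**What to change.** 1. Under Statistical analysis procedures, state that the recommended and partial groups are combined by number of infants: total cost divided by infants randomised in the arm. Infant-days are used only to build up quantities of staff time, medicines and consumables. Name the same weight under Site-wise and combined analysis plan.
2. Reconcile the two-day and three-day costing lengths for partial courses in RCT2, and say which trial and which cost items each length covers.
3. Where treatment days are recorded to apply the 80% rule, replace the assigned lengths by the observed mean days by group, arm and site, at least as a sensitivity analysis.

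The first two are changes of wording and a small spreadsheet change. The third depends on what was recorded: the article lists treatment duration as a data item only for the household sample, so full per-infant costing from recorded days may not be possible.
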